#### Acceptability/usability

Usability will be assessed in terms of the fidelity of the data. We will report proportional data loss for each of the secondary measures outlined below and as consistency/reliability of the captured data. A high proportional data loss or low reliability would indicate a need for revision of device designs or protocols in explaining their use. In terms of acceptability, we will pay particular attention to any difficulties that participants may face over the course of the study and conduct an informal discussion to gather opinions about potential improvements. However, because of the lack of expected depth in these responses, we do not intend to conduct formal qualitative analyses.

#### Secondary patient-centered outcome measures

Both secondary measures will be assessed before and after the intervention task administered in each session. All tasks are coded in OpenSesame 3.2.1 [40] and run on a Dell Inspiron 15 5000 series touchscreen laptop (1920 × 1080 resolution, 15.6″ screen). Hand/arm order was counterbalanced between administrations, within sessions (e.g. pre: L-R; post: R-L) and between tasks (e.g. finger tapping L-R; pointing R-L).

##### Finger tapping

Finger tapping performance is used routinely in clinical practice to assess the presence and severity of bradykinesia in people with PD but is often restricted to the count/number of taps, which provides only limited information (e.g. [41]). Objective, multivariate measures of tapping performance that quantify the speed and variability of performance as well as tap frequency are needed in addition to clinical assessment. Our measures of finger tapping are influenced by those collected from the recently developed BRAIN (BRadykinesia-Akinesia INcoordination) test, recently validated for assessment of bradykinesia in PD [42, 43]. At the beginning of the trial, the BRAIN test was not available for general use. As such, we collect detailed response data from the standard single-digit finger tapping task included as part of the UPDRS-III, using pairs of modified touchscreen gloves. These gloves are a practical, low-cost measurement device that preserves natural motion. Each contact of the conductive pads on the thumb and index finger registers as a left or right mouse click for the respective hand. Each trial begins with a 3-s countdown, followed by the word ‘TAP!’ which cues the action and stays on the screen for 15 s. Each hand will be tested separately with the wrist resting against the table and the other hand laid flat. Kinesia is measured as the number of taps over 15 s and the time between taps. The dwell time for each tap is collected, as a measure of akinesia. Lower values or increased variance for kinesia measures would reflect worse performance, indicating more motor fatigue, whereas lower values for akinesia measures would reflect less motor fatigue, as participants are able to reliably disengage from the movement. We will also be able to calculate a slope of performance for each hand as a profile measure for the number of taps per second as a more specific measure of fatiguing bradykinesia.

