### Secondary objective

Estimation of variance and effect sizes to inform power calculations for larger scale RCTs for primary and secondary outcome measures:A clinically relevant change in UPDRS-III motor examination scores of at least 5 points from pre to post measurements in response to spatial grid navigation training relative to the other control tasks.Improvement in movement kinematic response times over the course of the five intervention sessions in response to spatial grid navigation training relative to the other control tasks.Improvement in motor fatigue measures over the course of the five intervention sessions in response to spatial grid navigation training relative to the other control tasks.

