### Secondary outcome measures

*Motor fatigue*: Changes in the finger tapping count, the time between taps (kinesia measures) and tap dwell time (akinesia)*Motor slowing*: Changes in the response latencies (total movement time, movement initiation time and velocity) on the movement kinematic task

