##### Movement kinematics

In people with PD, movement kinematic measures of velocity and trajectory are impaired relative to healthy controls [44, 45] and changes in the measures in response to an intervention may index subtle targets for rehabilitative efforts. In our simple pointing task, participants must press down and hold a button on a custom-made USB response box for 4000 ms. Three red circles, 2° (102px, 57 cm) in diameter, are displayed in an arc at left [(− 750px, − 47px) ≈ (13°, 0.85°) from centre], centre [(0px, − 325px) ≈ (0°, 6°)] and right locations [(750px, − 47px) ≈ (13°, 0.85°) from centre]. Participants continue to hold down the response button until one of the circles turns green at a variable SOA of 750 ms, 1500 ms and 2250 ms. Participants will be instructed to make a reaching movement to touch the green target as fast and as accurately as possible, before returning their hand to the response box (they do not have to touch the button to end the trial). Each participant will wear a pair of touchscreen-compatible gloves to neutralise differences in skin conductivity. To minimise strain on the wrist, a mousepad with gel wrist support will be placed under the response box. There are 18 trials per hand. The primary outcome measure on this task is action completion time (touch response time − target onset time) and was the primary dependent variable in our pilot study using an analogue version of the task. The action completion time can be decomposed into two separate elements: movement initiation time (key release time − target onset time) and reaching time/velocity (touch response time − initiation time), which could reflect subtle targets for improvement of motor slowing in adults with PD. In addition, we collect measurements of accuracy of the touch response and deviation from the centre of the target on each trial as a measure of incoordination.

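### The tapping section gives both kinesia measures one direction (lower is worse), which is right for the tap count but reversed for the time between taps

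*Protocol article*

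**What the plan says.** Under Secondary outcome measures, motor fatigue is to be assessed by "Changes in the finger tapping count, the time between taps (kinesia measures) and tap dwell time (akinesia"), so the interval is grouped with the count and dwell time is kept apart. The Finger tapping section repeats the grouping: "Kinesia is measured as the number of taps over 15 s and the time between taps". The window is fixed, since the cue "cues the action and stays on the screen for 15 s".

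The same section then says how the values are to be read. For kinesia: "Lower values or increased variance for kinesia measures would reflect worse performance, indicating more motor fatigue". For dwell time the direction is reversed: "whereas lower values for akinesia measures would reflect less motor fatigue". The article nowhere exempts the time between taps from the kinesia direction.

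The measures serve a stated objective. The Secondary objective section seeks variance and effect-size estimates for, among other things, "Improvement in motor fatigue measures over the course of the five intervention sessions".

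For the pointing task, the Movement kinematics section splits action completion time into movement initiation time and a second part, given as "reaching time/velocity (touch response time − initiation time").

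**The concern.** Count and interval are two views of the same tapping rate. If one goes up because the patient taps faster, the other goes down, so a single statement that lower is worse cannot suit both. It suits the count.

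What is at stake is the meaning of improvement on a listed outcome. A reader or analyst who follows the sentence as printed would take a shorter interval after training as a sign of more fatigue, while taking the matching rise in count as a sign of less. The Blinding section has the analysis done with re-coded conditions, so the direction written down beforehand is what should guide interpretation until the codes are released.

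This is not detail that an article may leave to a fuller document. The direction is stated, and for one of the two measures it is stated wrongly.

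**Working it through.** **Inputs.** The window T = 15 s and the grouping of count and interval as kinesia come from the Finger tapping section, and Secondary outcome measures gives the same grouping. The article gives no tapping rates, so every interval, gap and dwell value below is an assumption used only to show direction. The plan has no figure of its own to reproduce.

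**Reading 1: time between taps runs from one contact to the next.** Count N ≈ T / interval.

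| Mean interval (s) | Taps in 15 s |
|---|---|
| 0.60 | 25 |
| 0.50 | 30 |
| 0.40 | 37.5 |
| 0.30 | 50 |
| 0.25 | 60 |

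The count rises as the interval falls, throughout the range. In the other direction, 30 taps gives 15/30 = 0.500 s and 45 taps gives 15/45 = 0.333 s. The count changes by 15/30 = +50% and the interval by (333 − 500)/500 = −33%. Under the printed direction the first is better and the second is worse, for the same performance.

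**Reading 2: time between taps is the gap from release to next contact.** N ≈ T / (gap + dwell). With dwell held at 0.10 s:

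| Gap (s) | Taps in 15 s |
|---|---|
| 0.50 | 25 |
| 0.40 | 30 |
| 0.30 | 37.5 |
| 0.20 | 50 |

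The direction is the same. The count fails to rise only if dwell lengthens by at least as much as the gap shortens. Take a gap falling from 0.40 to 0.30 s, with a starting dwell of 0.10 s and so 15/0.50 = 30 taps:

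- dwell rises to 0.15 s: 15/0.45 = 33.3 taps
- dwell rises to 0.20 s: 15/0.50 = 30 taps
- dwell rises to 0.25 s: 15/0.55 = 27.3 taps

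In the last case the deterioration lies in dwell, which the article already scores separately with the correct direction. This reading therefore does not rescue the sentence.

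**What is not affected.** The clause that more variance is worse holds for the interval. A mean change in milliseconds and its variance are computed from the raw data and do not depend on which direction is called better. Only the label attached to the sign does.

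**Pointing task.** The article defines completion = touch − onset and initiation = release − onset. If these two elements make up completion, the remainder is

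completion − initiation = (touch − onset) − (release − onset) = touch − release.

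The printed bracket, with touch on the same clock as in the completion formula, gives

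touch − (release − onset) = (touch − release) + onset,

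which equals reaching time only when onset is zero, that is, when touch is counted from target onset. The decomposition shows what is meant, but the bracket does not say it. The result is a duration with no distance in it, so velocity is a loose name for it.

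**The case against.** The strongest reply is that the sentence describes and does not score. It sets no reverse coding, threshold or decision. It can also be read sensibly as a lower count or more variable intervals, since a count is one number per trial and within-trial variance belongs to the intervals. An attentive analyst would probably notice the slip. The primary objective is feasibility, the primary clinical outcome is the UPDRS-III motor score, and Statistical methods promises mainly descriptive analysis with cautious interpretation.

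Much of this stands. The misreading depends on the sentence being applied literally, and it touches one component of one secondary outcome. The charitable reading, however, has to be supplied by the reader: the printed sentence speaks of kinesia measures in the plural, and the only reversal it offers is for dwell time.

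A reader might also infer three stronger things that the article does not support.

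- **That two outcomes carry the wrong sign.** Movement kinematics states no better or worse direction for velocity, Secondary outcome measures lists it among response latencies, and the Secondary objective speaks of response times. Its label and formula are loose, but no direction is reversed.
- **That a composite or a tally of improved measures would cancel out.** None is planned.
- **That the estimates passed to the larger trial are corrupted.** The raw interval estimates and variances are the same either way.

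**Conclusion.** The point holds in limited form. The stated direction is correct for tap count and wrong for the level of time between taps, under either reading of that interval. The conclusion needs only the fixed 15 s window and the article's own grouping. The 30-to-45-tap example (500 to 333 ms) is an assumption that shows direction, not the size of any effect in this trial.

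Taken literally, the error would apply to this measure for every participant, hand and session, but it concerns interpretation alone. Severity is minor to moderate. The pointing-task matter is a clarification of wording and adds nothing to the severity.

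**What to change.** In Finger tapping, replace the single kinesia direction with one per measure:

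- tap count: higher is better
- time between taps: lower is better
- variability: lower is better
- dwell time: lower is better

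In Movement kinematics, write reaching time as touch time minus key-release time, lower being better, so that it and initiation time sum to action completion time. Do not call this duration velocity, and align the entry under Secondary outcome measures.

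The cost is a few words. No data collection, analysis model or sample size changes. There is no need to promote the within-trial slope of tapping to the main fatigue measure; that would be a preference and does not follow from this error.

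### The finger-tapping section gives both kinesia measures the same direction (lower is worse), which is right for the tap count but reversed for the time between taps

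*Protocol article*

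**What the plan says.** The protocol article sets the direction of the tapping measures in the Finger tapping section, under the secondary patient-centred outcomes.

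- Kinesia, definition: "Kinesia is measured as the number of taps over 15 s and the time between taps".
- Akinesia, definition: "The dwell time for each tap is collected, as a measure of akinesia".
- Direction for kinesia: "Lower values or increased variance for kinesia measures would reflect worse performance, indicating more motor fatigue".
- Direction for akinesia: "whereas lower values for akinesia measures would reflect less motor fatigue, as participants are able to reliably disengage from the movement".

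The list under Secondary outcome measures groups the variables in the same way: "Changes in the finger tapping count, the time between taps (kinesia measures) and tap dwell time (akinesia". The grouping therefore appears in two places and is unlikely to be an artefact of how the text was extracted.

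Nowhere does the article exempt the time between taps from the kinesia direction, invert it, or convert it to a rate.

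**The concern.** A count and an interval taken from the same tapping record normally run in opposite directions: more taps in a fixed time means less time per tap. One direction cannot suit both. The stated one fits the count, so it is wrong for the interval. The article already treats its other time measure, dwell, as better when shorter, so the two time measures are given opposite directions.

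The time between taps is a listed secondary outcome. The Secondary objective seeks effect sizes for improvement in motor fatigue under grid navigation relative to the control tasks, and improvement needs a direction. The Finger tapping section is the only place that supplies one. The Discussion makes a formal power calculation for a larger trial depend on seeing the expected effects. Followed literally, the rule would report faster tapping as more fatigue on this outcome, and slower tapping as improvement.

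**Working it through.** The plan gives no figure to reproduce; the check is on direction.

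**Inputs from the article**
- Window: the cue to tap appears and "which cues the action and stays on the screen for 15 s", so T = 15 s.
- Grouping and directions: as set out above.

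**Assumed inputs.** The article gives no tap counts or dwell times. Counts of 20 to 60 and dwell times of 80 to 300 ms are used for illustration only.

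**Step 1. Interval from tap to tap.** If tapping fills the window, mean interval ≈ T / n, where n is the count.

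| Taps in 15 s | Mean interval |
|---|---|
| 20 | 15/20 s = 750 ms |
| 30 | 15/30 s = 500 ms |
| 45 | 15/45 s = 333 ms |
| 60 | 15/60 s = 250 ms |

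The interval falls as the count rises.

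**Step 2. Apply the stated direction to one change, from 30 to 45 taps.**

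| Measure | Before | After | Change | Reading under the article's sentence |
|---|---|---|---|---|
| Count | 30 | 45 | +15 | higher, so better |
| Interval | 500 ms | 333 ms | −167 ms | lower, so worse and more motor fatigue |

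The same record is read in two opposite ways. With a longer interval taken as worse, both measures show improvement. The estimate is 167 ms in absolute size either way; only its reading changes.

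**Step 3. Interval that excludes dwell.** The article does not say whether the time between taps runs from tap to tap or from release to the next contact. In the second case, gap ≈ T / n − dwell. With dwell held constant:

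| Assumed dwell | Gap at 30 taps | Gap at 45 taps |
|---|---|---|
| 80 ms | 420 ms | 253 ms |
| 120 ms | 380 ms | 213 ms |
| 160 ms | 340 ms | 173 ms |

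The gap still shortens as tapping speeds up, so the direction is still reversed.

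**Step 4. Where the relation can fail.**
- A large change in dwell can outweigh it. With 30 taps and 300 ms dwell, the gap is 500 − 300 = 200 ms. With 45 taps and 80 ms dwell, it is 333 − 80 = 253 ms. Count and gap then rise together.
- A participant who stops early loses count without a longer mean interval. Thirty taps at 333 ms take 30 × 333 ms ≈ 10 s, so stopping there gives a count of 30 with a mean interval of 333 ms, not 500 ms.

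These cases limit how tightly the two measures are tied. They do not make a shorter interval a sign of worse performance in general.

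**The case against.** The best defence is that the sentence is compressed. It names two criteria, lower values or increased variance. Within one 15 s trial the count is a single number, while the intervals form a distribution. The authors may have meant lower values for the count and greater variance for the intervals, and the same section asks for measures of both speed and variability. That may well be the intention. It is not what the sentence says, however: both criteria are attached to kinesia measures as a group, and the interval belongs to that group. The variance criterion itself is sound and should stay.

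It can also be said that an analyst who sees raw milliseconds beside a rising count is unlikely to call shorter intervals more fatigue, and that the planned taps-per-second slope is not made ambiguous by this sentence. Both points stand, and they lower the severity.

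A reader might infer more than the article supports:

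- **That this is a scoring rule, or that the two measures would cancel in a composite.** The sentence guides interpretation only. No score, composite or count of favourable outcomes is defined for tapping.
- **That the future sample size would be corrupted.** The variance and absolute effect size of the interval do not depend on which direction is called better. Only the sign and its interpretation do.
- **That count and interval must always disagree under the rule.** This depends on tapping filling the window and on how dwell is treated, as the limiting cases show.

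**Conclusion.** The point holds as an error of direction for one measure. The article's only stated direction for the time between taps is reversed. Read literally, a change from 30 to 45 taps (500 to 333 ms) is a gain on one kinesia measure and a loss on the other.

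The conclusion rests on the inverse relation between count and interval. That relation is close for tap-to-tap intervals filling the 15 s window, and it keeps its direction at similar dwell if the interval excludes dwell. The counts and dwell times are illustrative, but the direction does not depend on them.

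Severity is minor to moderate. It is probably a wording slip and concerns one component of a secondary outcome. The primary objective is recruitment and device usability, the primary clinical outcome is the UPDRS-III motor score, and the Statistical methods section plans mainly descriptive analysis with cautious interpretation. Recruitment, randomisation, sample size and the feasibility criteria are untouched. It is still worth correcting, because the text fixes the direction wrongly and does not merely leave it open.

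**What to change.** In the Finger tapping section, replace the shared direction with one for each measure, and keep the variance criterion:

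- fewer taps in 15 s: worse;
- longer time between taps: worse;
- greater variance: worse;
- longer dwell time: worse (this keeps the article's existing direction).

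State whether the time between taps includes dwell. Before analysis, confirm that the code and the results tables treat a fall in the interval as improvement.

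The cost is a reworded sentence, a short definition and a sign check. Data collection does not change.

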##### Movement kinematics

In people with PD, movement kinematic measures of velocity and trajectory are impaired relative to healthy controls [44, 45] and changes in the measures in response to an intervention may index subtle targets for rehabilitative efforts. In our simple pointing task, participants must press down and hold a button on a custom-made USB response box for 4000 ms. Three red circles, 2° (102px, 57 cm) in diameter, are displayed in an arc at left [(− 750px, − 47px) ≈ (13°, 0.85°) from centre], centre [(0px, − 325px) ≈ (0°, 6°)] and right locations [(750px, − 47px) ≈ (13°, 0.85°) from centre]. Participants continue to hold down the response button until one of the circles turns green at a variable SOA of 750 ms, 1500 ms and 2250 ms. Participants will be instructed to make a reaching movement to touch the green target as fast and as accurately as possible, before returning their hand to the response box (they do not have to touch the button to end the trial). Each participant will wear a pair of touchscreen-compatible gloves to neutralise differences in skin conductivity. To minimise strain on the wrist, a mousepad with gel wrist support will be placed under the response box. There are 18 trials per hand. The primary outcome measure on this task is action completion time (touch response time − target onset time) and was the primary dependent variable in our pilot study using an analogue version of the task. The action completion time can be decomposed into two separate elements: movement initiation time (key release time − target onset time) and reaching time/velocity (touch response time − initiation time), which could reflect subtle targets for improvement of motor slowing in adults with PD. In addition, we collect measurements of accuracy of the touch response and deviation from the centre of the target on each trial as a measure of incoordination.

### Intervention tasks

Target positions in the start and test grids of the tasks described below were identical across tasks. Five independent blocks of trials were generated and counterbalanced between sessions and participants using a 5 × 5 Latin square to mitigate any potential bias in the sequence generation process. Two blocks of 18 trials are administered with a self-paced break in between. All tasks were programmed in OpenSesame 3.2.1 [40]. To avoid contamination of motor fatigue and motor slowing measures, responses are made verbally in all three intervention tasks. Responses are recorded by OpenSesame via a small cardioid lapel microphone and stored as individual wave files. Response times are then extracted offline using the VoiceKey programme for Windows command line [46] or manually verified using Praat [47] in the case of any errors/noise spikes.

